## Abstract

**Background/Objectives:** Osteonecrosis of the femoral head is a progressive disease that frequently leads to femoral head collapse and secondary osteoarthritis. Although total hip arthroplasty provides reliable outcomes, its use in younger patients is limited due to concerns regarding implant longevity. Joint-preserving procedures such as core decompression have been widely used; however, their efficacy remains controversial. This study aims to evaluate a combined approach using arthroscopy-assisted core decompression and an osteoconductive bone substitute. **Methods:** This study is designed as a single-center, externally controlled trial conducted at Tohoku University Hospital. Patients with osteonecrosis of the femoral head (Japanese Investigation Committee Stage 1–3B, Type B–C2) will undergo arthroscopy-assisted core decompression combined with octacalcium phosphate/gelatin composite implantation. A total of 25 patients will be prospectively enrolled. Outcomes will be compared with a propensity score-matched historical control cohort. The primary outcome is disease progression within 1 year, defined as radiographic progression or conversion to total hip arthroplasty. Secondary outcomes include radiographic changes, clinical outcomes, and bone remodeling assessed by computed tomography. **Expected Results:** This study is expected to provide preliminary clinical evidence regarding the feasibility and potential effectiveness of arthroscopy-assisted core decompression combined with octacalcium phosphate/gelatin composite implantation for osteonecrosis of the femoral head. The intervention may promote bone remodeling and contribute to the prevention of femoral head collapse. **Conclusions:** The findings of this study may contribute to the development of improved minimally invasive joint-preserving treatment strategies for osteonecrosis of the femoral head and provide a basis for future large-scale clinical trials.

## 1. Introduction

Osteonecrosis of the femoral head (ONFH) is a common hip disorder characterized by femoral head collapse, which can lead to secondary osteoarthritis, resulting in severe hip pain and functional limitations [1]. In most cases, intraosseous necrosis has already occurred at the time of diagnosis, making early detection difficult, and patients are often asymptomatic before femoral head collapse, with spontaneous reduction in the necrotic area being rare and larger lesions more likely to progress to collapse [1,2]. A national epidemiological survey conducted in 2004 estimated that approximately 11,400 patients with ONFH were treated annually in Japan, with approximately 2200 new cases diagnosed each year [3]. Once femoral head collapse occurs, patients develop pain and gait disturbance, ultimately leading to irreversible deterioration of hip joint function, and many patients with ONFH require surgical treatment, with more than half undergoing surgery within nine months of diagnosis [4]. Total hip arthroplasty (THA) is indicated in advanced stages with substantial joint destruction and provides excellent pain relief and functional outcomes; however, complications such as infection and dislocation can occur, and long-term mechanical loosening may necessitate revision surgery [1,5,6]. Moreover, several studies have suggested that patients with ONFH may experience higher complication and revision rates after THA compared with those with primary osteoarthritis [7,8,9]. Because ONFH often affects relatively younger patients, the indication for THA should be considered carefully, and joint-preserving procedures are preferred before substantial joint destruction occurs [5,10]. Femoral osteotomy procedures, such as transtrochanteric rotational osteotomy and curved varus osteotomy, have been widely performed in Japan to transfer the viable portion of the femoral head to the weight-bearing area while shifting the necrotic region away from load-bearing zones [11,12]. However, these procedures are highly invasive, involving substantial disruption to bone, musculotendinous structures, and the joint capsule, and their utilization has shown a decreasing trend based on a Japanese nationwide database study [13].

Core decompression is a less invasive joint-preserving option. This procedure involves drilling into the necrotic area from the lateral femoral cortex to reduce intraosseous pressure and promote revascularization [10,14]. However, according to the Japanese Orthopaedic Association Guidelines for Osteonecrosis of the Femoral Head 2019, no consensus has been reached regarding the efficacy of core decompression (Recommendation grade 5, evidence level D), reflecting the limited and inconsistent clinical evidence as well as variability in reported outcomes across studies [11]. Recent systematic reviews and meta-analyses have suggested that core decompression may delay disease progression in selected patients with early-stage ONFH. Nevertheless, substantial heterogeneity among surgical techniques, adjunctive procedures, and patient populations precludes definitive conclusions regarding its efficacy [15,16]. Surgical treatments combined with core decompression include cell-based and growth factor therapies, such as bone marrow-derived mononuclear cells [17,18,19,20], bone marrow-derived mesenchymal stem cells [21], platelet-rich plasma [22], bone morphogenetic proteins (BMP-2 and BMP-7) used in combination with bone grafting [23,24,25], and fibroblast growth factor-2 (FGF-2) combined with core decompression [26]. Alternatively, core decompression combined with artificial bone grafting, such as β-tricalcium phosphate (β-TCP), has been reported, with favorable clinical outcomes [27,28]. Since femoral head collapse creates structural voids and instability within the necrotic region, filling these defects is considered biomechanically reasonable. β-TCP grafting has been reported to achieve outcomes comparable to vascularized fibular grafting [29] and to be less invasive than allogeneic bone grafting while remaining effective [30]. Octacalcium phosphate/gelatin composite (OCP/Gel) has demonstrated superior osteoconductivity compared with β-TCP mainly in preclinical studies, including animal experiments and in vitro investigations [31,32,33,34,35,36]. However, clinical evidence in humans remains limited. Recent transcriptomic analyses using comprehensive RNA sequencing have revealed that OCP/Gel exerts pro-angiogenic effects, suggesting that this material may enhance vascularization within the necrotic lesion and thereby contribute to bone regeneration [37]. It has been commercialized and may enhance bone regeneration, making it a promising material for defect filling. In addition, in pre-collapse stages, OCP/Gel may promote regeneration of the necrotic area and potentially prevent subsequent femoral head collapse. Therefore, this material may provide both regenerative and preventive benefits in the treatment of ONFH. Hip arthroscopy has been explored as a minimally invasive option for the management of ONFH, particularly in early-stage disease or in combination with core decompression; however, its role remains limited, and the current evidence is insufficient to establish its efficacy as a standalone treatment [38,39].

The aim of this study is to evaluate the efficacy and safety of arthroscopy-assisted core decompression combined with OCP/Gel implantation for patients with osteonecrosis of the femoral head. Specifically, this study will assess its potential to promote bone regeneration and prevent femoral head collapse, while enabling the simultaneous evaluation and treatment of intra-articular pathology.

## 2. Materials and Methods

### 2.1. Study Design

This study is a single-center, externally controlled trial. Patients undergoing artificial bone grafting will be compared with a historical cohort of patients with ONFH treated conservatively. Propensity score matching will be used to adjust for baseline differences. The flowchart of the study is shown in Figure 1.

This study was approved by the Tohoku Certified Review Board of Tohoku University (approval number: CRB2200003, approval date: 30 April 2025) and will be conducted in accordance with the Declaration of Helsinki. Written informed consent will be obtained from all participants in the prospective intervention cohort prior to enrolment. For the historical control cohort, the requirement for informed consent was waived by the ethics committee due to the use of anonymized retrospective data.

A randomized controlled trial was not feasible for this study due to the low incidence of ONFH, the novel nature of the intervention with no established efficacy data, and ethical considerations regarding withholding a potentially beneficial joint-preserving treatment from younger patients at risk of femoral head collapse. Therefore, this study was designed as a single-center, externally controlled pilot trial.

The trial has been approved by the institutional review board of the Tohoku Certified Review Board of Tohoku University (Ministry of Health, Labor and Welfare Certified Clinical Research Review Board, Tohoku University; approval number: CRB2200003) and is registered at jRCT (Japan Registry of Clinical Trial; jRCT1022250003; registration date: 21 May 2025, URL: https://jrct.mhlw.go.jp/re/reports/detail/10819122 (accessed on: 21 May 2025).

### 2.2. Population

We will include 25 patients with ONFH. As an external control, historical data will be extracted from patients previously diagnosed with ONFH and treated conservatively at Tohoku University Hospital. Eligible patients in the historical cohort must meet the following criteria: (1) diagnosis of ONFH based on radiographic and MRI findings at the time of initial presentation; (2) classification as Stage 1, 2, 3A, or 3B (excluding Stage 4) and Type B, C1, or C2 according to the criteria of the Japanese Investigation Committee (JIC) of Idiopathic Osteonecrosis of the Femoral Head [40]; (3) age ≥ 18 years at the time of diagnosis; and (4) no restriction on sex [41]. Eligible patients in the historical cohort will be selected to match the study population as closely as possible. Historical control data will be extracted from patients treated conservatively at Tohoku University Hospital between Jun 2005 and May 2021. During this period, radiographic and MRI-based diagnosis and staging were performed according to the Japanese Investigation Committee classification. Nevertheless, temporal changes in clinical practice and patient management may have influenced the outcomes and should be considered when interpreting the results.

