### 2.4. Exclusion Criteria

Patients will be excluded if they:(1)Have a history of hip surgery(2)Are pregnant or breastfeeding(3)Have ONFH secondary to trauma, tumor, or other specific diseases. Patients with steroid-induced or alcohol-related ONFH will be included because these etiologies represent common forms of non-traumatic ONFH.(4)Have contraindications to artificial bone materials.

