### 2.6. Evaluation Methods

**Primary outcome**

The primary outcome will be progression of ONFH within 1 year from baseline. Progression will be defined as the occurrence of either of the following events: (1) radiographic stage progression according to the classification system of the Japanese Investigation Committee of Idiopathic Osteonecrosis of the Femoral Head, or (2) conversion to total hip arthroplasty (THA). Baseline will be defined as the time of surgery in the intervention group and the time of initial diagnosis based on radiographic findings at Tohoku University Hospital in the historical control group. Radiographic stage progression will be assessed using anteroposterior radiographs obtained preoperatively and at 1 year. Collapse will be quantified by measuring the collapse length (mm), defined as the distance between the femoral head contour and a best-fit spherical outline on the femoral head. Radiographic evaluations, including assessment of disease progression and collapse length, will be performed independently by two orthopedic surgeons. Any discrepancies will be resolved by consensus. Because complete blinding to clinical information is difficult in this study, formal blinded assessment is not planned. In addition, formal assessment of interobserver agreement is not planned because of the exploratory nature of this pilot study.

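### Control eligibility rests on treatment received after the control group's time zero, and the plan gives no rule for controls who have hip surgery other than THA within the year

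*Protocol article*

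**What the plan says.** **Control definition.** Section 2.2 of the protocol article states that "historical data will be extracted from patients previously diagnosed with ONFH and treated conservatively at Tohoku University Hospital", and again: "Historical control data will be extracted from patients treated conservatively at Tohoku University Hospital between Jun 2005 and May 2021". Section 2.1 describes the comparison group in the same way. No time window is attached to conservative treatment.

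**Control time zero.** Section 2.6 sets baseline for controls at "the time of initial diagnosis based on radiographic findings at Tohoku University Hospital in the historical control group".

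**Primary outcome.** Section 2.6 counts either of two events within 1 year of baseline: "radiographic stage progression according to the classification system of the Japanese Investigation Committee of Idiopathic Osteonecrosis of the Femoral Head", or conversion to THA. No other operation is named.

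**Control criteria.** Section 2.2 lists four: imaging diagnosis, stage and type, age, and no restriction on sex. Section 2.4 excludes patients who "Have a history of hip surgery", and those with ONFH secondary to trauma, tumor or other specific diseases. The section 2.2 list does not repeat these exclusions.

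**Selection.** Section 2.2 adds: "Eligible patients in the historical cohort will be selected to match the study population as closely as possible". Section 2.10 separately specifies 1:1 propensity score matching on age, sex, body mass index, stage, type and etiology.

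**Background frequency.** The Introduction reports, for ONFH patients in general, "more than half undergoing surgery within nine months of diagnosis". It also says that osteotomy has been widely used in Japan, with a declining trend.

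**The concern.** Whether a past patient was treated conservatively becomes known only as the record unfolds after diagnosis. If the abstractor applies the label to the whole year, eligibility is conditioned on the post-baseline course, which is closely tied to the outcome. If the label is applied to the plan at diagnosis, the problem largely disappears, but the protocol does not say so.

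The endpoint adds a second gap. A control who has THA is an event. A control who has an osteotomy, a core decompression or another hip operation is an event only if stage progression is seen on a film. If the 1-year film is missing, the complete-case rule in section 2.10 removes that patient.

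The control progression rate is half of the primary comparison, and section 2.10 says that the study exists to supply progression rates and effect sizes for a later trial. Propensity matching on baseline covariates cannot repair selection on what happened afterwards. Prior hip surgery is neither a listed control criterion nor a covariate in the propensity model.

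**Working it through.** The plan states no control rate, effect size or power, so there is no figure to reproduce. The check has two parts.

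**1. Can the phrase be given one consistent meaning?**

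- *Never operated during the year.* This conflicts with section 2.6, because THA within the year is an event that controls are meant to contribute.
- *No operation other than THA during the year.* This fits the endpoint, but it removes controls on post-baseline information.
- *Non-operative plan at diagnosis.* This fits the endpoint and uses baseline information only. It is not stated, and it leaves non-THA surgery without a handling rule.

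**2. How far can the handling rule move the control rate?**

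Let T be the share of controls with THA, O the share with other hip surgery, and r the stage progression rate among unoperated controls.

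- (a) Any hip surgery counts as an event: T + O + (1 − T − O)r
- (b) Patients with non-THA surgery removed: [T + (1 − T − O)r] / (1 − O)
- (c) Non-THA surgery counted only through a film, and no film shows progression: T + (1 − T − O)r

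Rule (c) is a floor. Each such patient whose film does show progression moves the rate back towards (a).

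*Illustration on assumed counts.* Take 100 patients: 20 THA, 15 osteotomy, 15 stage progression without surgery, 50 stable.

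- (a) (20 + 15 + 15)/100 = 50%
- (b) (20 + 15)/85 = 41.2%
- (c) (20 + 15)/100 = 35%

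The same patients give 35% to 50%. The gap between (a) and (c) equals O, here 15 points. The gap between (a) and (b) is 50 − 41.2 = 8.8 points.

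*Range.* Set T + O = 0.50, borrowing the lower bound of the Introduction's figure. Let O run from 0.05 to 0.30 and r from 0.20 to 0.40. All three choices are assumptions.

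| Rule | Control rate | Shift from (a) |
|---|---|---|
| (a) | 60% to 70% | none |
| (b) | 43% to 68% | 2 to 17 points lower |
| (c) | 30% to 65% | 5 to 30 points lower |

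*Consequence.* At T = 0.30, O = 0.20 and r = 0.20 the rates are (a) 60%, (b) 0.40/0.80 = 50% and (c) 40%. Against an assumed 20% in the intervention group with 25 per group, approximate power is 0.85, 0.61 and 0.33. This is an unpaired approximation, because the plan gives no discordance for McNemar's test.

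*Scale.* With 25 patients and a rate of 50%, the 95% half-width is 1.96 × √(0.5 × 0.5/25) = 0.196. The 9 to 15 point shifts in the illustration are smaller than this sampling error but of the same order, and unlike it they are systematic.

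*Direction.* If the osteotomy patients were progressing, 50% is the relevant rate and (b) and (c) understate it, which works against the intervention. If none of them would have progressed, 35% is the relevant rate and removing them overstates it at 41.2%. The document does not settle which holds.

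**The case against.** The endpoint includes radiographic stage progression, so a reader who infers that every control with an osteotomy is either removed or scored as a non-event goes too far. Some would be events. That stands, and it is why 35% is a floor.

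A reader might also infer that every operated control is excluded, which would leave only the unoperated: 15/65 = 23% in the illustration. The documents do not support that, because THA is a control event.

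Nor does the Introduction show that more than half of these controls were operated on. Its figure covers ONFH patients in general, not Stage 1–3B patients managed conservatively at this hospital, and osteotomy use is said to be declining. It makes the problem plausible and does not size it.

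The sentence on selecting controls closely can be read as an introduction to the propensity matching in section 2.10. Section 2.4 is also not expressly limited to the prospective arm. Both readings are possible. But section 2.2 sets out the control criteria as its own list, and neither reading is stated.

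An article may leave abstraction rules to a fuller protocol. Here, though, the article itself states the control definition, time zero and endpoint, and together they make eligibility turn on post-baseline treatment. The limitations in the Discussion mention selection bias, differing treatment indications and the asymmetric baseline. They do not mention this dependence or non-THA surgery. Pilot status lowers the stakes for the hypothesis test, but not for the rate estimates that are the study's stated purpose.

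**Conclusion.** The point holds in a limited form. The control cohort is defined by treatment after its own time zero, the meaning of that treatment label is not fixed, and non-THA hip surgery within the year has no handling rule. The omitted exclusions and the informal selection sentence add to the room for choice in records whose outcomes already exist.

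The size in this cohort cannot be found from the document. The 35% to 50% range, and the wider ranges in the working, rest entirely on assumed counts. A reader might infer that the defect would manufacture a benefit. The documents do not support that: if operated controls are mostly progressors, the control rate is understated and the comparison is biased against the intervention. The true direction remains open.

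**What to change.** 1. In section 2.2, define controls as all consecutive patients in the stated period who meet section 2.3 items (2) and (3) and the applicable section 2.4 exclusions at the index date, and whose recorded plan on that date was non-operative. Keep them whatever followed.
2. Replace the sentence on selecting controls to resemble the study population with a reference to the propensity matching in section 2.10.
3. Lock the cohort and the matching before outcomes are extracted.
4. Keep the primary endpoint as stated in section 2.6. Making every hip operation a primary event would change the endpoint of a registered trial, and it is debatable because the Introduction treats osteotomy as joint-preserving surgery. Counting it as failure would raise the control rate and favour the intervention.
5. Prespecify non-THA hip surgery within 12 months as a named intercurrent event in both groups. Add a sensitivity analysis that counts it as progression, and report stage progression, THA and other hip surgery separately.

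The cost is protocol wording, abstraction rules and more chart work, since the plan at diagnosis must be read from each record. The control rate may change. No extra patients need to be enrolled.

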### 2.10. Statistical Analysis

As this study is designed as a pilot exploratory trial, a formal sample size calculation based on power analysis was not performed. A target sample size of 25 patients was determined based on the following considerations: (1) the rarity of ONFH, with an estimated annual incidence of approximately 2200 cases in Japan; (2) the novel nature of the intervention, for which no prior data are available to estimate effect size; and (3) the general recommendation that pilot studies should enroll at least 25 participants to provide a preliminary estimate of the effect size with sufficient precision for planning future confirmatory trials [44]. The findings of this study are intended to inform the design of future large-scale trials. Previous studies have reported that the progression rate of conservatively managed ONFH varies depending on disease stage and lesion size. The present pilot study is intended to provide preliminary estimates of progression rates and effect sizes, which will be used to inform sample size calculations for future confirmatory studies.

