Continuous variables will be expressed as mean ± standard deviation or median (interquartile range), as appropriate, and categorical variables as frequencies and percentages. The primary outcome (progression of ONFH within 1 year) will be compared between the intervention group and the historical control group. To reduce confounding due to the non-randomized design, propensity score matching will be performed. The propensity score will be estimated using a logistic regression model including age, sex, body mass index, disease stage, disease type, and etiology of ONFH. Information regarding corticosteroid use, alcohol consumption, concomitant medications, and year of diagnosis will also be collected. Because of the limited sample size and exploratory nature of this pilot study, these variables will not be included in the primary propensity score model to avoid overfitting but will be described and considered when interpreting the results. Patients will be matched 1:1 using nearest-neighbor matching with a caliper width of 0.2 times the standard deviation of the propensity score. Patients for whom an adequate match cannot be identified will be excluded from the matched analysis. This may reduce the effective sample size and limit the generalizability of the findings. Covariate balance after matching will be assessed using standardized mean differences, with values < 0.1 indicating adequate balance. After matching, paired categorical variables, including the primary outcome, will be analyzed using McNemar’s test. Secondary outcomes will be analyzed descriptively and compared between groups using appropriate statistical methods. Missing data will be handled using complete case analysis. Because the historical control cohort is derived from institutional databases with routinely collected clinical and imaging records, the amount of missing data is expected to be minimal. Therefore, complete case analysis was considered appropriate for this exploratory study. Because the amount of missing data is expected to be minimal, formal sensitivity analyses or multiple imputation procedures are not planned. Alternative approaches to missing data will be considered in future confirmatory studies if necessary. All statistical analyses will be performed using JMP version 19.0 (SAS Institute, Cary, NC, USA). A two-sided *p*-value < 0.05 will be considered statistically significant.

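### Section 2.2 allows an unspecified selection among eligible historical controls whose one-year outcomes are already on record; all eligible patients should enter the pool and the section 2.10 match should be the only selection step

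*Protocol article*

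**What the plan says.** Section 2.2 gives four criteria for historical controls: diagnosis, stage and type, age, and no restriction on sex. It then states: "Eligible patients in the historical cohort will be selected to match the study population as closely as possible". No variable, closeness rule or procedure is attached to that sentence. On the source it says: "Historical control data will be extracted from patients treated conservatively at Tohoku University Hospital between Jun 2005 and May 2021".

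Section 2.10 describes an algorithmic step. A logistic propensity model uses age, sex, body mass index, stage, type and etiology, and then: "Patients will be matched 1:1 using nearest-neighbor matching with a caliper width of 0.2 times the standard deviation of the propensity score". Balance is judged by standardized mean differences below 0.1, and the primary outcome is compared with McNemar's test.

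Section 2.6 defines the endpoint: "The primary outcome will be progression of ONFH within 1 year from baseline". An event is stage progression or conversion to total hip arthroplasty (THA). On reading the films it says: "Because complete blinding to clinical information is difficult in this study, formal blinded assessment is not planned". Section 2.1 dates the ethics approval ("approval number: CRB2200003, approval date: 30 April 2025").

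**The concern.** Without randomisation, the choice of which past patients serve as controls takes the place of allocation. The section 2.2 sentence is about patients who are already eligible, so as written a further selection follows eligibility. Nothing says that all or consecutive patients enter, and nothing equates this selection with the propensity match.

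The timing makes this matter. If May 2021 is the last diagnosis date, the last control's first year ended by about May 2022, roughly three years before the April 2025 approval. THA status and follow-up films are therefore already in the hospital's own records. The formal stage reading may still lie ahead, but it is not blinded, so it offers no protection.

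If entry to the pool were related to outcome, the later steps would not show it. Six covariates can be well balanced in a control group over-supplied with progressors or with non-progressors, and McNemar's test takes the pairs as given. The protocol intends the resulting rates and effect sizes to inform later sample size calculations, so a distorted control rate would carry forward even though this is a pilot.

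**Working it through.** **Inputs from the document.** Intervention group: "We will include 25 patients with ONFH". Matching is 1:1 with a caliper of 0.2 SD, and the test is McNemar's, two-sided at 0.05. There is no planning figure to reproduce, because "a formal sample size calculation based on power analysis was not performed".

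**Inputs assumed.** The document gives no control progression rate and no pool size. The rate p is taken as 20% to 70% and the pool as 50, 100 or 200. The treatment effect is zero throughout. Let r be the rate at which non-progressors enter the pool relative to progressors; r = 1 means that entry is unrelated to outcome.

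**Step 1: shift before matching.** The observed control rate is p / (p + (1 − p)r), and the spurious shift is that value minus p. For p = 0.40 and r = 0.8: 0.40 / (0.40 + 0.60 × 0.8) = 0.40 / 0.88 = 0.455, a shift of 5.5 points.

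| p | r = 0.8 | r = 0.67 | r = 0.5 |
|---|---|---|---|
| 20% | 3.8 | 7.2 | 13.3 |
| 30% | 4.9 | 9.0 | 16.2 |
| 40% | 5.5 | 9.9 | 17.1 |
| 50% | 5.6 | 9.9 | 16.7 |
| 60% | 5.2 | 9.1 | 15.0 |
| 70% | 4.5 | 7.7 | 12.4 |

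A shift of 10 points needs r of about 0.58 to 0.67, that is, 33% to 42% of non-progressors left out relative to progressors. Selection the other way reverses the sign: for p = 0.40 and r = 1.25, 0.40 / (0.40 + 0.60 × 1.25) = 0.348, a shift of −5.2 points.

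**Step 2: shift after matching.** This was simulated with 3,000 replicates per setting. One prognostic covariate stood in for the propensity score, the pool was thinned by outcome, and 1:1 nearest-neighbor matching with a 0.2 SD caliper followed. Across the three pool sizes the shift was −0.3 to +0.1 points at r = 1, 4.3 to 4.8 at r = 0.8, 8.1 to 8.3 at r = 0.67, and 14.3 to 14.5 at r = 0.5. Matching did not remove it.

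**Step 3: single substitutions.** With 25 pairs, one outcome-driven replacement of a control moves the difference by 1/25 = 4 points, and three move it by 12. With 20 pairs, each is worth 5 points.

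**Step 4: false positives.** McNemar's test was simulated on 25 independent pairs with p = 40% (200,000 replicates).

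| r | Asymptotic | Exact |
|---|---|---|
| 1 | 4.3% | 2.4% |
| 0.8 | 5.8% | 3.5% |
| 0.67 | 9.4% | 6.1% |
| 0.5 | 20.5% | 14.4% |

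**Scale.** The chance standard error of a 25 versus 25 difference is about 11 to 14 points for p between 20% and 60%.

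**The case against.** A reader might infer that controls will be picked by hand, in a separate step before the propensity match. The text does not say so. The sentence can be read as a loose summary of section 2.10, and the abstract, section 2.1 and Figure 1 all name propensity score matching as the method. That reading is as natural as the other. It does not remove the point, because no passage says that the two steps are one or that every eligible patient enters.

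A reader might also infer a bias above 10 points. Shifts of about 9.5 to 14 points do appear in simulations (assumed pools of 60, 120 and 250, about 40% progression) if five matched analyses are run on random halves of the pool and the most favourable is kept. Averaged over the five, the shift is −1.3 to +0.6 points, so narrowing the pool without regard to outcome creates no bias. The larger figure describes choosing the winner, which nothing in the document suggests is planned.

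A condensed article may leave the random seed and the processing order of the match to the analysis plan, so their absence is no fault. The study is an exploratory pilot, and its Discussion concedes potential selection bias from the historical control. That concession is general and does not mention selection with outcomes known.

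Finally, the sentence may do useful work. The four control criteria omit the section 2.4 exclusions, such as previous hip surgery and ONFH secondary to trauma or tumor, and this is the only text that aligns controls with the study population on them. That objection stands, and the replacement has to carry those exclusions.

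**Conclusion.** The point holds as a wording weakness that leaves open a route to bias; it is not evidence that bias will occur. As written, section 2.2 permits selection among eligible controls whose one-year outcomes are already on record, and the planned checks would not reveal it. The timing rests on May 2021 being the last diagnosis date.

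The size depends on assumed selectivity. Mild selection (r = 0.8) is worth about 4 to 6 points, well inside chance error. Strong selection (r = 0.5) is worth about 12 to 17 points before matching, similar to or larger than one standard error. The direction is also open: the text does not say whether progressors or non-progressors would be favoured. This is a worthwhile and inexpensive improvement under either reading of the sentence.

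**What to change.** In section 2.2, replace the selection sentence with:

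> *All consecutive patients diagnosed in the window who meet the control criteria, including those section 2.4 exclusions that can be ascertained from baseline records, enter the control pool; the propensity score matching in section 2.10 is the only selection step.*

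In section 2.10, add:

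> *The control pool and matched list are fixed on a baseline-only extract before 1-year films and THA status of controls are extracted or read, and this match is the primary one.*

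Seed and processing order can go in the analysis plan. With r = 1 the simulated shift is about zero, and McNemar's test keeps its usual false-positive rate.

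The cost is wording plus splitting the control extraction into a baseline file and a later outcome file, with no extra patients or procedures. The downside is that the locked match must be kept even if some outcome data later prove incomplete.
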